**INTRODUCTION**

---

This study is a multi-centre, prospective, randomised double-blind parallel-group comparison of long acting somatostatin analogue (Octreotide LAR) and placebo.

The study is coordinated by the Clinical Research Center for Rare Diseases of the Mario Negri Institute for Pharmacological Research, Ranica, Bergamo and will be conducted with the cooperation of:

- Hospital '*Ospedale San Giovanni di Dio*', Agrigento, Italy;
- Clinical Research Center for Rare Diseases '*Aldo e Cele Daccò*', Ranica (Bergamo), Italy
- Hospital '*Ospedale Vito Fazzi*', Lecce, Italy
- Hospital '*Ospedale Maggiore Policlinico, Mangiagalli e Regina Elena*', Milan, Italy
- University '*Università Federico II*', Naples, Italy
- Hospital '*Ospedale Ca' Foncello*', Treviso, Italy

Eligible patients will be stratified for the presence (YES or NO) of concomitant clinical conditions that could appreciably affect the rate of renal function loss over time including diabetes mellitus, 24 hour urinary protein excretion >1g, or any other evidence of concomitant renal disease without indication for specific therapy. Within each stratum patients will be randomized on a 1:1 basis to Long-acting Somatostatin (Octreotide LAR) 40 mg (treatment group) or saline solution (placebo group). Data will be collected by means of an *ad-hoc* study Case Report Form (see Appendix 1).

The general aim of the trial is to assess the efficacy of one year treatment with long-acting somatostatin analogue (Octreotide LAR) compared with placebo in slowing kidney and liver growth rate in patients with ADPKD and moderate/severe renal insufficiency (estimated GFR by MDRD 4 variables: 15-40 ml/min/1.73m^2) and to assess whether and to which extent this translates into slower renal function decline over 3-year follow-up.

Primary objectives are the followings: to compare the effect of long acting somatostatin analogue (Octreotide LAR) versus placebo on total kidney volume (TKV) change (delta TKV) as assessed by spiral computed tomography (spiral CT)

scan (short-term, one year) and to compare the effect of long-acting somatostatin analogue (Octreotide LAR) vs. placebo on the rate of GFR decline as assessed by serial measurements of the iohexol plasma clearance (long-term, three years).

The secondary objectives are to compare, among the two groups, absolute and relative changes in renal and liver volume parameters (at month 0, 12 and 36) as well as in functional and biochemical parameters by quarterly clinical visits during the 36 month follow-up. In particular, the following parameters will be assessed:

- Total kidney volume (at 3-years)
- Total renal cyst volume\*
- Total renal parenchyma volume\*
- Total renal intermediate volume\*
- Total liver and liver cyst volumes\*

*\*When feasible, by minimized radio contrast agent administration during CT acquisition*

- GFR decline (as assessed by serial measurements of the plasma iohexol clearance at month 0 and, every 6 months thereafter)
- Slope of eGFR (by MDRD 4 variable equation)
- Progression to the combined end point of doubling of serum creatinine and/or ESRD (*ESRD: need for chronic renal replacement therapy by dialysis or transplantation established on the basis of standard clinical criteria*)
- Progression to ESRD considered as a single endpoint
- Systolic, diastolic and mean blood pressure
- 24 h urinary protein excretion rate (at month 0 and every six months thereafter)
- Urinary osmolality (assessed from urine sodium, urea and glucose concentration on 24 hr urine samples)
- Morning spot urine sample (proteins, albumin, creatinine)
- Serum Insulin Growth Factor-1 (IGF-I)
- 24 h urinary phosphorus, creatinine and creatinine clearance
- Gallbladder sand/stones and renal stones (by ultrasonography).

In a subgroup of patients referred to the Clinical Research Center for Rare Diseases 'Aldo e Cele Daccò' and/or other institutions where these evaluations are feasible the

following other secondary objectives are to compare, among the two groups the quality of life and the societal costs by submitting to consenting patients a *Quality of life (QoL) Questionnaire* - Version 1 of SF-36 (QoL SF-36 V1™ Questionnaire) validated in Italy – and a *Short-Form-Health and Labour Questionnaire (SFHLQ)*. (See Appendix 2).

Furthermore, for exploratory purposes only, the treatment effect on endothelin and MCP-1 urinary excretion rate (overnight urine sample), in a subgroup (pending on study findings and fund availability).

This statistical analysis plan will be reviewed at the blind review of the ALADIN 2 data and modifications in light of the study conduct considered in line with the recommendations in the International Conference on Harmonization (ICH) guideline, ‘Statistical Principles for Clinical Trials E9’ (ICH (1998)). The above statistical plan is inspired to the ALADIN trial report (Caroli 2013), due to the analogies with ALADIN 2 study design.

## SECTION 2

### STUDY CONDUCT

---

#### 2.1 ANALYSIS POPULATIONS

Several analysis populations will be used:

##### **Full Analysis Set**

This set will consist of all patients randomised to receive study medication in the ALADIN 2 study.

##### **Per-Protocol Set**

This set will include all patients randomised to receive study medication in the ALADIN 2 study. All patients who have major protocol violations (see Paragraph 2.3) will be excluded.

##### **Safety Set**

This set will consist of all patients who received at least one dose of study medication.

A decision regarding the exact composition of the Per-Protocol Set will be made at the 'blind review' stage.

The efficacy analysis will be performed on both the Full Analysis Set and the Per-Protocol Analysis Set. The analysis performed on the Full Analysis Set should be considered the primary one.

The safety analysis will be performed on the Safety Set.

## 2.2 PATIENT ACCOUNTING

Individual patient randomisation details will be presented in Appendix 21.

Patient accounting details will be presented in Table 1.1. This table will provide numbers of patients in each of the analysis populations and the number of patients per site.

An outline of the treatment phase is described in the flow chart of the study (Appendix 3).

Table 1.2 will show the numbers of patients remaining in the study, in each treatment group and overall, at each of the follow-up time points, for the Full Analysis Set and the Per Protocol Set.

The reasons for withdrawal will be summarised in Table 1.3, by treatment group and overall. In addition, an individual patient data listing of trial-end details will be provided in Appendix 4.

## 2.3 PROTOCOL VIOLATIONS

The following are defined to be major protocol violations.

- Age <18 years
- Absence of clinical diagnosis of ADPKD
- Absence of ultrasound diagnosis of ADPKD
- Written Informed consent not given
- Presence of symptomatic biliary tract lithiasis
- Presence of active cancer
- Presence of psychiatric disorders or any condition that might prevent full comprehension of the purposes and risks of the study
- Presence of pregnancy, lactation or child bearing potential and ineffective contraception

During follow-up:

- Temporary withdrawal for at least 30 consecutive days or total amount of temporary withdrawal days more or equal to 20% of total duration of treatment phase
- Study duration less than 3 months when the main reason for discontinuation is: unsatisfactory efficacy, unsatisfactory compliance, protocol violation, lost of follow-up, withdrawal of consent. Patients who discontinued due to adverse event or death are *not* considered as major protocol violators.
- Breaking the blind code after randomization.

All remaining violations are to be considered minor protocol violations.

An individual patient data listing of all detected protocol violations (major and minor) will be provided in Appendix 5, identifying major protocol violations which resulted in the exclusion of the patient from the Per Protocol Set. Tables 1.4.1 and 1.4.2 summarize how often different types of violations occurred.

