### **3.3 EFFICACY ANALYSIS**

Primary efficacy analysis at one year is referred to TKV absolute change from time 0 (Visit 2) to 12 months (Visit 7). Primary efficacy analysis at three years is referred to the measured GFR slope from time 0 (Visit 2) onward.

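### The single per-protocol set has no month-12 cut-off, so later interruptions or code breaks remove valid 12-month TKV values from the supportive 1-year analysis

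*Supplement*

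**What the plan says.** Section 2.1 of the SAP defines one Per-Protocol Set, and exclusion from it is of the whole patient: "All patients who have major protocol violations (see Paragraph 2.3) will be excluded". The set is not tied to any endpoint: "The efficacy analysis will be performed on both the Full Analysis Set and the Per-Protocol Analysis Set". The note after Table 3.2 in the table templates repeats all Section 3 tables for this set. Tables 3.1.1 to 3.1.3 hold the 1-year and 3-year TKV p-values together, so one population serves both.

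The 1-year endpoint is fixed in section 3.3: "Primary efficacy analysis at one year is referred to TKV absolute change from time 0" to month 12.

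Section 2.3 lists three major violations during follow-up:

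- Interruption: "Temporary withdrawal for at least 30 consecutive days or total amount of temporary withdrawal days more or equal to 20% of total duration" of the treatment phase.
- Early end of study: "Study duration less than 3 months when the main reason for discontinuation is: unsatisfactory efficacy, unsatisfactory compliance, protocol violation, lost of follow-up, withdrawal of consent". This one carries its own time limit.
- Unblinding: "Breaking the blind code after randomization".

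The first and third have no limit at month 12.

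Two statements in section 2.1 bound the matter: "The analysis performed on the Full Analysis Set should be considered the primary one", and "A decision regarding the exact composition of the Per-Protocol Set will be made at the 'blind review' stage". The Introduction adds that the SAP itself will be reviewed at that stage.

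**The concern.** A per-protocol analysis of a month-12 measurement should depend on what happened up to that measurement. Here membership depends on events up to month 36. An interruption or code break in month 30 cannot have influenced a CT taken at month 12, yet it removes that CT from the 1-year analysis. The supportive estimate is then conditioned on post-endpoint events. If those events were related to treatment or to disease course, agreement or disagreement with the Full Analysis Set would be hard to interpret.

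There is a weaker concern in the other direction. If the 20% limit is scaled to three years, it is a loose filter on exposure in the one year that matters for TKV.

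**Working it through.** The SAP states no figure that could be reproduced here, so the check is a reading of the rules followed by arithmetic on the SAP's own day counts.

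**Inputs.** Section 2.4 sets 12 months at 365 days and 36 months at 1095 days. Section 2.3 gives the 30-day and 20% limits. The yearly interruption rates and the 28-day gap length below are assumptions, because the documents give neither. The length of the treatment phase in days is not stated either.

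**Step 1: trace one patient.** Full treatment to month 12, valid CT at months 0 and 12, one 30-day gap in month 30.

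- Section 2.3: 30 consecutive days is a major violation.
- Section 2.1: a major violation removes the patient from the Per-Protocol Set.
- Section 2.1 and the table note: that set is used for the 1-year TKV tables.
- Result: the 12-month value is lost, although the gap is only 30/1095 = 2.7% of three years. A code break in month 30 has the same effect.

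Of the 36 months in which these rules operate, 36 − 12 = 24 months, or two-thirds, lie after the CT.

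**Step 2: illustrate the size.** Let p be an assumed yearly probability of a first gap of 30 or more days, with every patient followed to month 36. The share of randomised patients whose first violation falls after month 12 is [1 − (1 − p)³] − p.

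| p per year | 1 − (1 − p)³ | minus p | dropped for events after month 12 |
|---|---|---|---|
| 0.05 | 0.1426 | 0.05 | 9.3% |
| 0.10 | 0.2710 | 0.10 | 17.1% |
| 0.15 | 0.3859 | 0.15 | 23.6% |

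For each rate these are upper figures. They assume that nobody leaves follow-up, everyone has a month-12 CT, and nobody is excluded for another reason. With an entry eGFR of 15 to 40 and ESRD among the withdrawal reasons in Table 1.3, the real share at a given rate would be smaller.

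**Step 3: the cumulative limit, if the treatment phase is 1095 days.**

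- 0.20 × 1095 = 219 days.
- 0.20 × 365 = 73 days.
- Three separate 28-day gaps in year 1 make 3 × 28 = 84 days, which is 84/365 = 23.0% of year 1 and 84/1095 = 7.7% of three years. No gap reaches 30 days and 84 is below 219, so the patient stays in. Over year 1 alone, 84 exceeds 73 and the patient would be excluded.
- As an outer bound, 218 days off drug in year 1 (218/365 = 59.7%) could escape both limbs if split into eight gaps of at most 29 days. This is arithmetically possible; nothing suggests it is typical.

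If the treatment phase means one year, the limit is already 73 days and this step largely falls away.

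**The case against.** The strongest reply is that the SAP does not treat the set as final. Its composition is decided at blind review, the SAP may be revised then, and Appendix 5 will list the violations that led to exclusion, so a post-month-12 exclusion would be visible. This stands in part: the problem can be mended before unblinding. But no rule by time point is given, and the only written rule excludes the patient from everything.

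A second reply concerns timing. The SAP does not say when the 1-year analysis is run. On a month-12 data cut, later events could exclude nobody. That is possible, but no such cut is described, and the templates place the 1-year and 3-year results in one table for one set.

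A third reply concerns the 20% rule, and most of it stands. The denominator is not given in days, the flow chart that might settle it is not shown, and the Introduction speaks of one year of treatment for kidney growth. The 40 rows on the drug administration form suggest dosing well beyond month 12 but do not define the phase. If dosing did end at month 12, only the code-break rule could act afterwards. Nor does the SAP say how days of temporary withdrawal are counted for a long-acting injection. On an assumed 28-day interval, counting one missed injection from the previous dose to the next gives 2 × 28 = 56 days. That already breaches the 30-day limb, so the three-gap example would not arise from missed doses. A reader might infer that heavily unexposed patients routinely stay in the 1-year set. The documents do not support this: any single gap of 30 days or more is already a major violation.

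**Conclusion.** The point holds for the supportive analysis. As written, one whole-patient Per-Protocol Set with no month-12 cut-off is applied to the 12-month TKV change, so events after the CT remove valid 12-month data. This follows from the text alone, given dosing or blinding that continues past month 12. The secondary point on scattered year-1 gaps holds only if the treatment phase is read as 1095 days and days off drug are counted gap by gap.

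How many patients are affected is unknown. The figures of about 9%, 17% and 24% rest wholly on assumed rates and full follow-up.

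Two stronger readings are not supported. A reader might infer that the 1-year primary result is compromised; it is not, because the Full Analysis Set is primary and these rules do not touch it. A reader might also infer that the selection favours one arm. A difference in interruptions or code breaks between an active drug and placebo is possible, but no passage gives rates by arm, and the background section of the quality-of-life protocol describes good tolerability in previous work. The change should be made because the stated rule selects on post-endpoint events, not because a bias of known size or direction has been shown.

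**What to change.** Define per-protocol membership by endpoint in sections 2.1 and 2.3.

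- For the 1-year TKV analysis, count follow-up violations only up to the date of the month-12 CT, with the 20% rule computed over that same period.
- For the measured GFR slope and other 3-year outcomes, keep the current rule over the full treatment phase.
- State the length of the treatment phase in days and how days of temporary withdrawal are counted.
- Tie the cut-off to the CT date and not to a visit number: section 3.3 calls month 12 Visit 7, while the templates for Tables 1.2 and 3.3.1 call it Visit 6.
- Show both sets in Tables 1.1 and 1.4.1.

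The cost is SAP wording and one extra population flag. Injection dates and CT dates are already on the case report form, so no new data are needed. The change should be settled no later than the blind review.

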## **2.4 COMPLIANCE AND ADHERENCE TO STUDY SCHEDULE**

Compliance details, in terms of temporary withdrawal, will be listed in Appendix 11.

The differences between actual and scheduled timing of each of the visits will be summarised in Table 1.5. The following schedule in relation to the differencing of dates will be adopted:

|                      |                       |
|----------------------|-----------------------|
| One week = 7 days,   | One month = 30 days,  |
| 3 months = 91 days,  | 6 months = 183 days,  |
| 9 months = 274 days, | 12 months = 365 days, |

|                        |                       |
|------------------------|-----------------------|
| 15 months = 456 days,  | 18 months = 548 days, |
| 21 months = 639 days,  | 24 months = 730 days, |
| 27 months = 821 days,  | 30 months = 913 days, |
| 36 months = 1095 days. |                       |

The following acceptable time windows in relation to the differencing of dates will be considered:

|                             |                           |
|-----------------------------|---------------------------|
| One week = 4-10 days,       | One month = 20-40 days,   |
| 3 months = 61-121 days,     | 6 months = 153-213 days,  |
| 9 months = 244-304 days,    | 12 months = 335-395 days, |
| 15 months = 426-486 days,   | 18 months = 518-578 days, |
| 21 months = 609-669 days,   | 24 months = 700-760 days, |
| 27 months = 791-851 days,   | 30 months = 883-943 days, |
| 36 months = 1065-1125 days. |                           |

### SECTION 3

## STATISTICAL METHODS

---

### 3.1 BASELINE SUMMARIES

The baseline visit is Visit 2 (Time 0). Summary statistics will be tabulated by treatment group, to assess the comparability of the groups, and overall, to describe the patient population (Full Analysis Set and Per Protocol Set), for the following parameters:

- Age, Gender, Race, Weight, Smoke, Alcohol, Coffee/tea, Marital Status, Education, Professional Status overall (Table 2.1.1) and according to stratum: CCC absent (Table 2.1.2) and to stratum: CCC present (Table 2.1.3)

- Vital signs: Blood Pressure (systolic and diastolic), Pulse Rate, Weight, Mean Arterial Pressure (defined as  $\frac{2}{3}$  diastolic blood pressure plus  $\frac{1}{3}$  systolic blood pressure) and ECG results overall (Table 2.2.1) and according to stratum: CCC absent (Table 2.2.2) and to stratum: CCC present (Table 2.2.3)
- TKV, height-adjusted TKV, overall (Table 2.3.1) and according to stratum: CCC absent (Table 2.3.2) and to stratum: CCC present (Table 2.3.3)
- mGlomerular Filtration Rate (m = measured) measured by iohexol plasma clearance (Table 2.4.1) overall and according to stratum: CCC absent (Table 2.4.2) and to stratum: CCC present (Table 2.4.3)
- eGlomerular Filtration Rate (e = estimated) using the 'four variable' abbreviated MDRD formula:  $GFR = 186 \times (SCR)^{-1.154} \times (Age)^{-0.203} \times (0.755 \text{ if female}) \times (1.210 \text{ if African-American})$  (Table 2.5.1) overall and according to stratum: CCC absent (Table 2.5.2) and to stratum: CCC present (Table 2.5.3)
- eGlomerular Filtration Rate (e = estimated) using the CKD-EPI equation (Levey 2009): if female and serum creatinine  $\leq 0.7$  mg/dl:  $144 \times (0.993)^{Age} \times (Scr/0.7)^{-0.329}$ ; if female and serum creatinine  $> 0.7$  mg/dl:  $144 \times (0.993)^{Age} \times (Scr/0.7)^{-1.209}$ ; if male and serum creatinine  $\leq 0.9$  mg/dl:  $141 \times (0.993)^{Age} \times (Scr/0.7)^{-0.411}$ ; if male and serum creatinine  $> 0.9$  mg/dl:  $141 \times (0.993)^{Age} \times (Scr/0.7)^{-1.209}$  (Table 2.6.1) overall and according to stratum: CCC absent (Table 2.6.2) and to stratum: CCC present (Table 2.6.3)
- Serum creatinine (Table 2.7.1) overall and according to stratum: CCC absent (Table 2.7.2) and to stratum: CCC present (Table 2.7.3)
- Hematochemistry: Urea, Sodium, Potassium, Calcium, Phosphorus, GOT, GPT, GGT, Alkaline phosphatase, total bilirubin, Direct Bilirubin, glucose, HbA1c, Uric Acid, Total Proteins, Albumin, IGF1 (Tables 2.8.1-2.24.1) overall and according to stratum: CCC absent (Tables 2.8.2-2.24.2) and to stratum: CCC present (Table 2.8.3-2.24.3)
- Lipid profile: Total cholesterol, HDL cholesterol, LDL cholesterol, Triglycerides (Tables 2.25.1-2.28.1) overall and according to stratum: CCC absent (Tables 2.25.2-2.28.2) and to stratum: CCC present (Table 2.25.3-2.28.3)

- Hemochrome: Leukocytes, Platelets, Erythrocytes, Hemoglobin, Hematocrit (Tables 2.29.1-2.33.1) overall and according to stratum: CCC absent (Tables 2.29.2-2.33.2) and to stratum: CCC present (Table 2.29.3-2.33.3)
- 24 Hours Urine collection: Proteins, Creatinine, Creatinine Clearance, Sodium, Urea, Glucose, Phosphate, Osmolality (Tables 2.34.1-2.41.1) overall and according to stratum: CCC absent (Tables 2.34.2-2.41.2) and to stratum: CCC present (Table 2.34.3-2.41.3)
- Spot Morning Urine: Proteins, Albumin, Creatinine, Protein-to-creatinine ratio, Albumin-to-creatinine ratio (Tables 2.42.1-2.46.1) overall and according to stratum: CCC absent (Tables 2.42.2-2.46.2) and to stratum: CCC present (Table 2.42.3-2.46.3)
- Previous Diseases (Table 2.47.1) overall and according to stratum: CCC absent (Table 2.47.2) and to stratum: CCC present (Table 2.47.3)
- Previous Medication/Non-Drug Therapy (Table 2.48.1) overall and according to stratum: CCC absent (Table 2.48.2) and to stratum: CCC present (Table 2.48.3)
- Concomitant Diseases (Table 2.49.1) overall and according to stratum: CCC absent (Table 2.49.2) and to stratum: CCC present (Table 2.49.3)
- Concomitant Medication/Non-Drug Therapy (Table 2.50.1) overall and according to stratum: CCC absent (Table 2.50.2) and to stratum: CCC present (Table 2.50.3)

For 'continuous' variables (e.g. age) the statistics presented will be mean(sd), median, Q1, Q3, minimum, and maximum and number of patients. For categorical variables (e.g. gender) frequency counts and percentages will be provided. Diseases will be summarised by MedDRA preferred term and medication/non-drug therapy will be summarised by ATC class (level 2), in terms of frequency counts and percentages.

Individual patient data listings of demographic data, previous diseases, concomitant diseases, previous medication/non-drug therapy and concomitant medication/non-drug therapy will be presented in Appendices 6 to 10 respectively.

### **3.2 ANALYSIS SPECIFICATIONS**

Assumptions underlying all parametric analyses will be checked and transformations to normality (e.g. log-transformation) or non-parametric methods used, where violations of assumptions are seen.

For efficacy analyses based on the Full Analysis Set, no imputation of missing values will be performed. The last available data value will be used to calculate the time to onset of an event.

For both the analyses based on the Full Analysis Set and the Per Protocol Set, visit windows will not be used and data points will be classified according to the named (nominal) visit.

All statistical tests will be two-sided unless otherwise stated.

